**Discussion:**

It is expected that the Pilates exercises will be more effective than aerobic exercises in improving clinical outcomes and that this improvement will be maintained over the medium to long term. This study aims to clarify whether the Pilates method can be incorporated into the clinical practice of physical therapists treating patients with fibromyalgia. The study will also provide information on which exercise will be most cost-effective, information that can be used by insurers and public health systems.

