## Background

Fibromyalgia is a rheumatologic disease characterized by chronic generalized pain, hyperalgesia, and allodynia [1]. It is also characterized by the presence of symptoms such as fatigue, sleep disorders, morning stiffness, headache, and paresthesia [1]. It can be classified clinically, following the diagnostic criteria of the American College of Rheumatology 2010 [2]: 1) Widespread Pain Index (WPI), calculated by adding up the number of areas in which the patient reported pain in the last week; and 2) Severity of Symptoms (SS), calculated by adding up the severity of fatigue, waking unrefreshed, cognitive symptoms and somatic symptoms [2]. To be classified as having fibromyalgia, a patient must present the following three clinical conditions: WPI ≥ 7 and SS ≥ 5 or WPI between 3 and 6 and SS ≥ 9 points; presence of symptoms at the same intensity for at least three months; and no disease/condition that could be the cause of the pain [2]. One of the main pathophysiological mechanisms of fibromyalgia is central sensitization, defined as increased responsiveness of nociceptive neurons in the central nervous system to their normal or subthreshold afferent input [3]. In this case, pain can arise spontaneously or be elicited by a normally innocuous stimuli (allodynia), is exaggerated and prolonged in response to a noxious stimuli (hyperalgesia), and spreads beyond the site of injury (secondary hyperalgesia) [4].

The average global prevalence of fibromyalgia is 2.7%, with a higher incidence in women (3:1) [5, 6]. In Brazil, this prevalence is 4.4% in the population aged 35–60 years [7] and 5.5% in people over 65 years of age [8]. Economic impact studies show that patients with fibromyalgia are significant consumers of health services and generate significant costs related to loss of productivity [9]. The average annual cost of fibromyalgia is estimated at approximately 6000 Canadian dollars [10], approximately 2,827,000 Yen of indirect cost and 1,943,000 Yen of direct cost in Japan [11], and this cost is even higher in European patients, approximately 8000 to 13,000 Euros per year [12, 13].

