### Economic assessment

Cost-effectiveness and cost-utility analysis will be carried out to evaluate the incremental cost per life-years adjusted for the quality (QALYs) of the interventions. The Fibromyalgia Impact Questionnaire will be used for cost-effectiveness analysis, and the EQ-5D-3L and SF-6D questionnaires will be used for cost-utility analysis. The costs measured in this study using resources by the participants will be: direct costs, which correspond to the costs of this participant to the public and private healthcare systems and the participant’s out-of-pocket expenses; and indirect costs through loss of productivity due to fibromyalgia. This assessment will be performed by information from a cost diary that the participants will keep at home. Three, six, nine, and 12 months after randomization, the assessor will collect these data by telephone. Thus, the costs of the interventions and the participants’ own expenses will be identified, measured, and validated. Table 2 shows the types of resources evaluated and the data sources from which the proposed information and evaluation methods will be taken. The number of work absences will be multiplied by the average salary rate to estimate the costs of paid work leave. Bus and subway fares or the price of fuel will be used to estimate transportation costs. Sensitivity analysis will test uncertainty in key parameters, such as the selection of cost weights and statistical variation in quality of life scores.

**Table 2 Tab2:** Assessment of the resource used

Resource type	Assessment tool	Assessment method	Sources consulted
Physical therapy sessions	Physical therapist report	Wage rates	Physical therapy board fee schedule
Medications, visits to doctors and/or health professionals of the public and private health systems, hospital stay, visits to emergency medical services	Questionnaires every three months	Published prices (costs for public and private health systems) and/or actual costs to participants	Pharmaceutical websites and medical services fee schedule
Visits to community or alternative services or alternative health professionals	Questionnaires every three months	Actual costs to participants	Health services fee schedule
Loss of productivity (assessed for hours of lost work)	Questionnaires every three months	Average wage in the state of Sao Paulo per hour for women and men	Brazilian Institute of Geography and Statistics website

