The cost-effectiveness analysis will be performed using the impact of fibromyalgia as outcome, and the cost-utility analysis using QALYs. Mean between-group cost differences will be calculated for total and disaggregated costs. Seemingly unrelated regression analyses will be performed in which effect and cost differences will be corrected for their baseline values if available, while also taking into account the possible correlation between effects and costs [54]. Incremental cost-effectiveness and cost-utility ratios will be calculated by dividing the corrected difference in total costs by the difference in effects. Uncertainty surrounding the cost differences and incremental cost-effectiveness and cost-utility ratios will be estimated using Bias Corrected and Accelerated bootstrapping techniques (5000 replications). The latter will be graphically presented in cost-effectiveness planes [55]. Cost-effectiveness acceptability curves will be estimated to indicate the intervention’ probability of being cost-effective compared with other at different values of willingness-to-pay [56]. The economic evaluation will be performed using STATA V.14.

In addition, a survival analysis will be performed to evaluate the number of sessions necessary for a 30% pain reduction compared to the initial pain, and this value was chosen because it is considered a minimal clinically significant difference in pain in patients with fibromyalgia [57]. This analysis will be performed using the Kaplan-Meier method [58] and the comparison between the groups by the Log-Rank test [59]. All analyses will follow the intention-to-treat principle. The significance level will be set at 5%. Table 3 shows the timeline of the study.

**Table 3 Tab3:** Timeline for the schedule of enrollment, interventions, and assessments

Outcomes	Enrollment	Before randomization	Intervention period (8 weeks)	8-week follow-up after randomization	6-month follow-up after randomization	12-month follow-up after randomization
Eligibility criteria	X					
Demographic data	X					
Informed consent	X					
Primary outcome						
Fibromyalgia impact		X		X		
Secondary outcomes						
Fibromyalgia impact					X	X
Pain intensity	X	X	X	X	X	X
Kinesiophobia		X		X	X	X
Specific disability		X		X	X	X
Health-related quality of life		X		X	X	X
Sleep quality		X		X	X	X
Functional capacity		X		X		
Interventions						
Aerobic exercise			X			
Pilates exercise			X			

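### No costing perspective is named and the only incremental ratios specified use total costs, although insurers and public health systems are named as users of the result

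*Protocol article*

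**What the plan says.** All references are to the protocol article.

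- **Costs measured (Economic assessment, Table 2).** Direct costs are "direct costs, which correspond to the costs of this participant to the public and private healthcare systems and the participant’s out-of-pocket expenses". Lost work is added as "indirect costs through loss of productivity due to fibromyalgia". For travel, "Bus and subway fares or the price of fuel will be used to estimate transportation costs".
- **Ratios (Statistical analysis).** "Incremental cost-effectiveness and cost-utility ratios will be calculated by dividing the corrected difference in total costs by the difference in effects". The bootstrap and the cost-effectiveness planes follow these ratios, and no other cost base is named for the acceptability curves.
- **Breakdown (Statistical analysis).** "Mean between-group cost differences will be calculated for total and disaggregated costs", with bootstrap uncertainty around the cost differences.
- **Users (Discussion of the abstract, repeated in the main Discussion).** The finding on which exercise is most cost-effective is described as "information that can be used by insurers and public health systems".

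No section names the perspective of the economic evaluation. The sensitivity analysis in Economic assessment gives cost weights and variation in quality-of-life scores as examples. It does not mention a change of perspective.

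**The concern.** The cost base of the specified ratios is wider than the cost base of the users the article names. An insurer or a public health system pays for sessions, visits, medication and hospital care. It does not, on the plain meaning of the article's own categories, pay for a participant's out-of-pocket spending or lost wages.

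If the arms differ in those other components, the total-cost ratio can differ from the payer's ratio in size, and it can also differ in sign. An exercise programme that costs the health system more could be reported as cost-saving overall because of fewer lost work hours, and the reverse is equally possible. The plan would then give the named users a cost-effectiveness plane and an acceptability curve that answer a different question from theirs.

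**Working it through.** The article states no cost or QALY difference, so there is no figure of the plan to reproduce. The check has three steps.

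**1. Cost base of the ratio.** Write the between-arm differences as H (health-system costs), O (out-of-pocket and transport), P (lost productivity) and E (effect). On the natural reading, total costs are H + O + P. The Statistical analysis section does not itemise them, so this is an inference from Economic assessment and Table 2.

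- Total-cost ratio = (H + O + P) / E
- Health-system ratio = H / E
- Gap = (O + P) / E

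The two agree only if O + P = 0. They have opposite signs whenever O + P is opposite in sign to H and larger in absolute size.

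**2. Illustration with assumed values.** None of these values comes from the documents, and the money unit is arbitrary. Take E = 0.02 QALY, H = +300 and O = +50, and vary P. The health-system ratio is 300 / 0.02 = 15,000 in every row.

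| P | H + O + P | Total-cost ratio |
|---|---|---|
| +400 | 750 | 750 / 0.02 = 37,500 |
| 0 | 350 | 350 / 0.02 = 17,500 |
| -200 | 150 | 150 / 0.02 = 7,500 |
| -350 | 0 | 0 |
| -600 | -250 | -250 / 0.02 = -12,500 (dominant) |

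With H and O at these values, the sign changes at P = -(300 + 50) = -350.

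**3. What a payer could recover from the planned output.**

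- *Point ratio:* recoverable, if the breakdown isolates health-system costs, by dividing that cost difference by the reported effect difference.
- *Plane and acceptability curve:* not recoverable. At a willingness to pay of k per unit of effect, the net benefit is k·E - H, with variance k²·Var(E) + Var(H) - 2k·Cov(E, H). The covariance between effects and health-system costs is not among the planned results. If H is the sum of several cost categories, Var(H) also needs the covariances between them. The article itself uses seemingly unrelated regression because effects and costs may be correlated.
- *The breakdown itself:* Table 2 places medication, visits, hospital stays and emergency care in one row, valued by published health-system prices and/or by what participants actually paid. A breakdown by resource type can therefore leave payer money and participant money mixed.

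**The case against.** The case on the other side is substantial.

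- **An all-cost ratio is an ordinary choice.** The Background motivates the study partly by lost productivity, and the stated aim is not limited to payers. This stands: the total-cost analysis is not an error and can inform a public decision-maker.
- **The article says only that payers can use the information.** It promises no payer-perspective ratio, and it also addresses physical therapists and patients. This stands too, and it is why the point is an improvement and not a contradiction.
- **A second perspective is the kind of detail a condensed article may leave to a fuller plan, and the sensitivity analysis is open-ended.** This stands in part. The point does not rest on silence alone: a numerator is stated and users are stated, and the two do not match.
- **A health-system ratio pools public and private payers.** This stands and is taken up in the fix.

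Three stronger readings are tempting and are not supported.

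- A reader might infer that the plan cannot tell payers anything about their own costs. The planned disaggregated differences, with bootstrap uncertainty, rule that out.
- A reader might take the Japanese figures in the Background, "approximately 2,827,000 Yen of indirect cost and 1,943,000 Yen of direct cost in Japan", and infer that productivity makes up 2,827,000 / (2,827,000 + 1,943,000) = 59% of the ratio's numerator. That share describes the average annual cost of the illness. It says nothing about the share of a difference between two active exercise arms.
- A reader might infer that the ratio is driven by the noisiest cost component. The article gives no variance for any cost category.

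**Conclusion.** The point holds as a gap between the specified ratios and the users named for them. No perspective is stated, both ratios are specified on total costs alone, and no plane or acceptability curve is specified on the costs that insurers or public health systems bear. From the planned output a payer could obtain at most a point ratio, without its joint uncertainty.

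The size for this trial is unknown. The illustration shows only that size and sign can change; it does not show that they will. The conclusion rests on two assumptions: that total costs contain every component listed in Economic assessment and Table 2, and that the named payers do not bear out-of-pocket and productivity costs. The primary outcome, its analysis and the sample size are unaffected.

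**What to change.** In Statistical analysis:

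1. Keep the total-cost analysis, itemise what total costs contain, and name the perspective.
2. Add a second run of the same seemingly unrelated regressions, ratios, bootstrap, planes and acceptability curves restricted to health-system costs, meaning intervention sessions and health-service use without out-of-pocket, transport and productivity costs.
3. Separate participant-paid amounts from health-system amounts in the mixed row of Table 2. Where the data allow, show public and private payers separately.
4. State that any conclusion addressed to insurers or public health systems rests on the second analysis.

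Settling this before results are known also prevents the perspective from being chosen by its answer. The cost is some extra coding of who paid, a second run, and two sets of ratios to report. If the diaries and telephone questionnaires do not record who paid, the separation in item 3 will be incomplete, and the report should say so.

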## Discussion

Until the moment, this is the most robust and least biased study about the effectiveness of the Pilates method as a treatment resource for patients with fibromyalgia, comparing it with aerobic exercise. It is also the first study to investigate the cost-effectiveness of two different modalities of therapeutic exercise. Current evidence shows that aerobic exercise does not generate very good adherence in the treatment of patients with fibromyalgia [60], although it has a low to moderate effect on the improvement of their symptoms [16]. Pilates method can lead to greater adherence [61] because it uses equipment and exercises divided into levels of progression. Pilates exercises may cause less muscle soreness and may be more pleasurable and stimulating, which would facilitate its implementation in patients with fibromyalgia who tend to be resistant to exercise. Finally, there is little information on the long-term effects of different exercise modalities for patients with fibromyalgia, and this study will monitor these patients for one year.

This study aims to clarify whether the Pilates method can be incorporated into the clinical practice of physical therapists treating patients with fibromyalgia, as well as which exercises to use and how these exercises can be performed. An easy-to-replicate protocol for aerobic exercise in these patients, with adequate training intensity and frequency, will also be described, as well as information about muscle soreness pain and progression of exercises in each exercise modality. The study will also provide information on which exercise will be most cost-effective, information that can be used by insurers and public health systems. With this study, patients will know whether the Pilates method can be used as an alternative treatment and which exercise modality causes less pain.

The study took all measures to minimize the risks of methodological bias, that is, it was prospectively registered, and it has a relevant sample, concealed allocation, intention-to-treat analysis, and blinded assessor. It allows generalization of the data for the majority of patients with fibromyalgia. In addition, it has pragmatic interventions, with Pilates exercises being performed as in clinical practice, with individualized exercises according to the clinical conditions of the participants each day, without a fixed protocol. The aerobic exercise will be prescribed following the recommendations of the most recent systematic reviews [16, 25] and the American College of Sports Medicine [44], respecting the individuality and clinical condition of each participant by monitoring exercise intensity. The physical therapists responsible for the interventions have clinical experience in the prescription of the respective exercises. The study has as a limitation the non-blinding of participants and therapists, and this limitation stems from the type of intervention (physical exercise).

## Abbreviations

EQ-5D-3L: Euroqol 5 dimensions
HR: Heart rate
HRmax: Maximum heart rate
QALY: Quality adjusted life years
SF-6D: Short-form 6 dimensions
SS: Severity of symptoms
WPI: Widespread pain index
